#### Data storage

REDCap Cloud (www.redcapcloud.com), a secure Part 11 Validated Electronic Data Capture application, is managed by trained study staff at SDRI and used to hold all records and sociodemographic, biometric, psychosocial, and wearable participant data. Data may be collected in the following ways: recorded on hard copy or electronic source documents by study staff and Especialistas, securely extracted from partnering medical clinic Electronic Health Record system, and self-collected by participants via wearable devices. Study participant identity is protected by assigning participants a unique identifier upon enrollment. All data used in the analysis and reporting is de-identified and will not contain any Protected Health Information. No identifiable patient information will be released. Access to the cloud-based Mil Familias database is restricted to those SDRI researchers who have been granted permission by the Mil Familias research team.

Participants who drop out during the screening are recorded as screening failures in the participant’s file and no further follow-up is required. The data is included in the study database and is reported. An individual participant is to be withdrawn from the study if the participant withdraws consent for study participation, without the need to justify the decision. All data is included in the study database and is reported.

#### Data analysis

Statistical analyses will be performed in collaboration with SDRI’s data partner, Santa Barbara Actuaries, Inc. All statistics will be considered significant with *p* values < 0.05. Chi squared tests will be conducted to detect differences in categorical outcomes. T-tests will be conducted to test differences in continuous outcomes where the sample size is less than 50 for any sub population. Z tests will be conducted for continuous variables with a sample size greater than 50 where there is no evidence of violation of normality. For continuous outcomes that may violate the normality assumption, a log-normal transformation or other appropriate analysis may be applied.

In addition, independent variables may be confounders of each other’s effect on the outcomes and thus consideration will be given to explore likely confounders. There are adjustment approaches, such as propensity score matched cohorts, to address such biases. Regression analysis for a particular outcome can also be performed on various individual characteristics.

Based on the experience from the Operational Pilot, we expect the sample size of the full study to be sufficient to provide substantial levels of statistical significance to compare the relationship between outcomes and individual variables. For example, based on the Operational Pilot (*n* = 107), HbA_1c_ can be stratified into 2 groups (> 9 and < 7%). In the Pilot, we found that 40% had an HbA_1c_ < 7%, and for 28% it was > 9%. This was significant at the 3% level and this will fall below 1% with 160 participants and below 0.1% at 280. Our full study population is designed to have 1000 members, so we believe that the majority of individual variables of interest will be powered to show statistically significant conclusions.

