### Setting and participants

In Santa Barbara County, the population is 45.6% Latino, most of Mexican ancestry [8]. To establish the Mil Familias cohort, up to 1200 families may be screened and enrolled with an estimated 20% screen-fail or dropout rate, resulting in approximately 1000 families in the study. Potential participants are selected from Santa Barbara County and surrounding communities or satellite sites with the help of existing community allies and healthcare organizations. Approaches to recruitment include engagement with and referrals from: local Federally Qualified Health Centers (FQHCs); community service providers; academic institutions with high English as a Second Language enrollment (i.e., Hispanic Serving Institutions); local employers; local media (Spanish and English language); social media; advertisements; participation in community events; SDRI physical site and websites; and ad hoc interaction with Especialistas. This type of combined approach was successful in the operational pilot. Only participants who meet all eligibility criteria are enrolled and study staff confirm participant eligibility during the screening and enrollment encounter. A “family” is followed as one unit, but is estimated to include on average 3 to 5 individuals (based on findings from the operational pilot). Therefore, up to 6000 individuals may be screened and enrolled.

The definition of “Mil Familias family” accounts for statistical, tracking, and reporting requirements of this study and is based on the U.S. Census definition of a “family group” and modified to include single-person units and relatedness via domestic partnership [9]. Each individual may participate in just one Mil Familias family. A “Mil Familias family” consists of an enrolled individual family representative and any enrolled family members. The family representative is the first enrolled. A family member is any individual subsequently enrolled who: (a) resides with the family representative (i.e., co-resides) and (b) is an immediate relative (spouse/partner, parent, child, or sibling) to the family representative by birth, marriage/domestic partnership, or adoption.

**Inclusion Criteria** (family representative)

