### Study activity series and scheduling encounters

Study activities take place through face-to-face interaction between families and study staff; these visits are referred to as “encounters.” Encounters are organized into “series,” with activities varying based on whether the series is for a new participant or a continuing participant. Each new participant completes an initial encounter series, including screening/enrollment and informed consent, Health Promotion Assessment (HPA), laboratory tests, questionnaires, and reflection, as well as physical activity monitoring and interaction with the Especialista with whom they are paired. After having been enrolled in the study for at least 12 months, participants are eligible to start the continuing participant encounter series. The continuing participant encounter series involves activities similar to the new participant encounter series. While continuing participation is preferred, it is not required to be eligible for the study.

In the course of this 3-year protocol, participants will complete at least 1 new participant encounter series and, possibly, 0, 1, or 2 continuing participant encounter series, depending on their initial enrollment date. Regardless of series type (new participant or continuing participant), participants have the flexibility to complete encounters in accordance with their personal schedules as long as encounter series are completed in chronological order. The last encounter, Reflection, in a 12-month participation cycle occurs at least 3 months after the HPA encounter.

Families may attend study encounters as a group, but individual data collection and informed consent occurs one-on-one in a private setting, unless the participant is a minor. As detailed above, participants are assigned to a data collection group based on their age and diabetes status.

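### The named chi-squared, t and z tests assume independent observations, but the cohort enrols co-resident relatives, so association p-values using several members per family are wrong

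*Protocol article*

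**What the plan says.** The Data analysis section of the protocol article names the tests in committing language:

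- Categorical outcomes: "Chi squared tests will be conducted to detect differences in categorical outcomes".
- Continuous outcomes, small groups: "T-tests will be conducted to test differences in continuous outcomes where the sample size is less than 50 for any sub population".
- Continuous outcomes, larger groups: "Z tests will be conducted for continuous variables with a sample size greater than 50", provided normality is not in doubt.
- Threshold: "All statistics will be considered significant with" p below 0.05.

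Three softer provisions follow. Propensity-score matching is mentioned as a way to deal with confounding. Regression is optional and concerns individuals: "Regression analysis for a particular outcome can also be performed on various individual characteristics". The only clause that opens the door to another method is tied to distributional shape: "For continuous outcomes that may violate the normality assumption, a log-normal transformation or other appropriate analysis may be applied".

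The sampling structure is set out under Setting and participants. A family "is estimated to include on average 3 to 5 individuals", its members live with the family representative and are immediate relatives, and the family is tracked as a single unit. Single-person units are allowed. On timing, Study activity series and scheduling encounters says "After having been enrolled in the study for at least 12 months, participants are eligible to start the continuing participant encounter series", so one person may contribute one to three series.

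**The concern.** Members of one household share address, income, food environment and often genes, and each family is paired with an Especialista. Their outcomes can be expected to correlate. The design builds this dependence in, and the protocol says its family definition serves statistical requirements among others. The analysis text then makes no use of the family.

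Two opposite errors follow. For a determinant shared by the household, such as income, the tests count relatives as separate evidence, and p-values are too small. For a comparison inside families, such as the member with T2D against the member without, the shared family component cancels from the difference. The tests do not know this, so p-values are too large and power is lost.

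Both kinds of question are central to the stated objective, which concerns five groups of determinants in Latino families. Over 100 variables are to be collected per person, so a distorted error rate would recur across many tests.

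**Working it through.** **The plan's own figure.** The protocol gives no ICC, design effect or error rate for clustered data, so there is none to reproduce on this exact point. Its one worked example is from the pilot: 40% with HbA1c below 7% and 28% above 9% among 107 people, stated as significant at 3%. The only counts that round to these percentages are 43 and 30. Treated as two independent samples of 107, with unpooled variance and a one-sided test:

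- difference = 43/107 − 30/107 = 0.1215
- z = 1.89, p = 0.029, matching the stated 3%.

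The example therefore also rests on an independence calculation and carries no allowance for clustering. It shows only how the section reasons. The pilot enrolled adults with T2D, and nothing is said about how many shared a household.

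**Inputs.** Mean family size 3 to 5 (Setting and participants). Test level 5%, taken as two-sided because the document does not say. ICC of the outcome within family: not in the documents, assumed 0.1 to 0.4. Number of contributing members m: 4 as the middle of the stated range, and 2 because Tables 1 and 2 show many instruments, including food security, given to adults only. The value 2 is illustrative.

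**1. Determinant constant within the household.** Design effect D = 1 + (m − 1) × ICC; true type I error = 2 × [1 − Φ(1.96/√D)].

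| m | ICC | D | True type I error |
|---|---|---|---|
| 2 | 0.1 | 1.1 | 6.2% |
| 2 | 0.4 | 1.4 | 9.8% |
| 4 | 0.1 | 1.3 | 8.6% |
| 4 | 0.4 | 2.2 | 18.6% |

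With m = 4, 1000 families supply 4000 people but the information of 4000/1.3 = 3077 down to 4000/2.2 = 1818 independent people.

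**2. Exposure varying both within and between families.** D is approximately 1 + (m − 1) × ICC of exposure × ICC of outcome. With m = 4:

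- both ICCs 0.2: D = 1 + 3 × 0.04 = 1.12, true error 6.4%
- both ICCs 0.3: D = 1 + 3 × 0.09 = 1.27, true error 8.2%.

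**3. Contrast inside families.** If every family has the same split between the two groups, the variance factor is 1 − ICC:

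- ICC 0.1: 1.96/√0.9 = 2.07, true error 3.9%
- ICC 0.4: 1.96/√0.6 = 2.53, true error 1.1%.

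A comparison that would have 80% power with the correct standard error (noncentrality 2.80) has Φ(2.80 − 2.07) = 77% at ICC 0.1 and Φ(2.80 − 2.53) = 61% at ICC 0.4.

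**Simulation check.** With 1000 families of 4 and ICC 0.3, the naive test rejected in 15.3% of null data sets for a household-level exposure (formula 15.5%) and in 1.8% for a within-family exposure (formula 1.9%).

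**The case against.** The strongest reply has four parts.

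- **The article is a condensed account.** Clustering might be handled in a fuller plan, and regression and matching are already foreseen. This does not answer the point. The article does more than leave the method open: it says which tests will be run, and they do not suit the sample. The regression is optional and described only for individual characteristics, matching addresses confounding, and the clause on other analyses concerns non-normality.
- **Family size overstates the contributing cluster.** This stands. Food security and most questionnaires are for adults only, HbA1c is optional in children, and single-person units exist. The figures for m = 2 are often the relevant ones. BMI and waist circumference are taken in all four groups, so the larger cluster can apply there.
- **Most exposures are neither purely household-level nor purely within-family.** This also stands. The intermediate case gives about 6% to 8%, so the upper end of the household-level range is not the typical error.
- **The primary outcome is creation of the cohort.** No test bears on it. Correct, and this limits the severity.

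A reader might also infer that annual series on one person will be pooled as independent records, or that change over time will be tested unpaired. The document does not say so. It names no longitudinal method, but t-tests may be paired, and continuing series are optional. Repeated series raise the same problem only if they are pooled or compared unpaired, so no error rate is attached to them here.

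**Conclusion.** The point holds for household clustering. Applied as written to several members per family, the named tests give p-values that are too small for household-level determinants and too large for within-family contrasts. The size depends on an ICC that the documents do not give, so the percentages illustrate a range and do not estimate this cohort's error. Any positive ICC produces the same directions; a value near zero would make the error negligible.

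The fault is confined to secondary and association analyses that use more than one member per family. An analysis restricted to one person per family at one time point is sound in this respect. The remedy lies in the analysis and leaves recruitment and measurement alone, so this should be fixed but does not threaten the establishment of the cohort. Severity: should-fix.

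**What to change.** For every inferential analysis using several members per family, replace the simple tests with one of the following, stated in advance:

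- linear or logistic mixed models with a family random intercept; or
- GEE, or regression with family-clustered robust standard errors.

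Add a person-level term wherever more than one annual series enters the analysis. For determinants that vary inside families, enter the family mean and the individual's deviation from it separately, so that between-family and within-family effects are not mixed. Keep the chi-squared, t and z tests for descriptive tables.

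The cost is revised analysis wording, standard software and a family identifier in the analysis file. The article documents a participant identifier. A family link is implied by tracking the family as a unit but is not described, so its presence in the database should be confirmed. Intervals for household-level factors will be somewhat wider.

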### Major secondary outcomes

These include (a) achieved HbA_1c_ levels; (b) cardio-metabolic risk including blood pressure, waist circumference, and insulin sensitivity; (c) food security; and (d) activity levels. Details of additional secondary end-points have been published previously (https://clinicaltrials.gov/ct2/show/NCT03830840).

In addition to the variables listed above, we also collect prospective data related to major cardiovascular events (3-point MACE: cardiovascular death, non-fatal myocardial infarction and non-fatal stroke). Data sources include participants and their families, collaborating health centers, and the local provider of in-hospital clinical care. At enrollment, participants provide written, informed consent for Mil Familias researchers to request data from the relevant provider organization’s electronic medical record system on reported clinical events. Additional information are collected on new onset diabetes including gestational diabetes, unscheduled attendances at emergency rooms, and hospital admissions due to uncontrolled diabetes.

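### The general chi-squared rule, if applied to the prospective yes/no events, ignores follow-up of under one to three years and can show a false association wherever follow-up is linked to the exposure

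*Protocol article*

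**What the plan says.** **Test.** Under Data analysis, the protocol article sets significance at p below 0.05 and states "Chi squared tests will be conducted to detect differences in categorical outcomes". Regression and propensity-score matching are mentioned as possibilities, with no commitment and no link to time at risk. The section does not mention censoring, incidence rates or time-to-event methods.

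**Events.** Under Major secondary outcomes, after the four listed outcomes, the article adds: "we also collect prospective data related to major cardiovascular events". It also collects information on "new onset diabetes including gestational diabetes, unscheduled attendances at emergency rooms, and hospital admissions due to uncontrolled diabetes". No test is named for any of these. The sources are participants, families, health centres and the local hospital's records, with consent for record access given at enrolment.

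**Follow-up.** Under Study activity series and scheduling encounters, a participant in the 3-year protocol completes one initial series and then possibly "0, 1, or 2 continuing participant encounter series, depending on their initial enrollment date". Continuation is voluntary: "While continuing participation is preferred, it is not required to be eligible for the study". The closing Reflection encounter may come as early as three months after the health assessment. Under Primary outcome, data collection runs for up to three years.

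**Entry order.** Under Setting and participants, the family representative is enrolled first and relatives afterwards.

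**The concern.** Whether someone has had a cardiovascular event or developed diabetes by the end of the study depends on the risk per year and on the years observed. A chi-squared test on the proportion with an event sees only the product of the two. If one exposure group was observed for longer, it shows more events even when the yearly risk is the same.

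The stated objective is the influence of the five determinants over time, so event comparisons across social, behavioural and psychological exposures are a natural use of these data. The article offers two plausible routes from exposure to follow-up. Relatives enter after the representative, so entry date can track family role. Voluntary continuation may also depend on work, insurance or trust, all of which are recorded as exposures. The article does not show that either route operates, but its analysis rule gives no protection if one does.

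A secondary point concerns new-onset diabetes. HbA1c is first measured after enrolment, and the Background stresses undiagnosed diabetes in this population. The article does not say how diabetes first found at that test is to be distinguished from diabetes that develops later.

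**Working it through.** The article gives no event rate, event count or power for these events, so there is no stated figure to reproduce.

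**Inputs from the article:** 5% significance level (sidedness not stated; two-sided used here); maximum follow-up three years; one cycle can close three months after the health assessment, so someone with no continuing series can have under one year.

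**Assumed inputs:** constant hazard h of 0.01 to 0.03 per year, identical in both groups; independent individuals; group sizes as shown.

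**Step 1: apparent risk under equal hazards.** Risk over T years is 1 − exp(−hT). With h = 0.02 and 500 per group, using the normal formula for two proportions:

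| Follow-up (years) | Risks | Apparent risk ratio | Chi-squared rejects |
|---|---|---|---|
| 1.75 vs 1.75 | 3.4% vs 3.4% | 1.00 | 5% |
| 1.5 vs 2.0 | 3.0% vs 3.9% | 1.33 | 13% |
| 1 vs 2 | 2.0% vs 3.9% | 1.98 | 44% |
| 1 vs 3 | 2.0% vs 5.8% | 2.94 | 88% |

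For example, 1 − exp(−0.02 × 1) = 0.0198 and 1 − exp(−0.02 × 3) = 0.0582, with ratio 2.94. The apparent risk ratio is close to the follow-up ratio although the true hazard ratio is 1.

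**Step 2: follow-up that varies within both groups.** Step 1 gives everyone in a group the same follow-up, which is too stark. In a simulation (4000 runs per setting), follow-up T is uniform from 0.25 to 3 years, and the probability of being in group 1 is 0.5 + a(T − 1.625)/1.375. Here a = 0 means no link; a = 0.2 gives mean follow-up of about 1.8 vs 1.4 years, and a = 0.4 about 2.0 vs 1.3.

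The comparator is a person-time test, z = (d₁ − Df)/√(Df(1 − f)). Here d₁ is the number of events in group 1, D the total number of events and f the share of person-time in group 1.

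| h per year | Total n | Mean follow-up | Chi-squared rejects | Person-time test rejects |
|---|---|---|---|---|
| 0.01 | 1000 | equal | 5.0% | 5.0% |
| 0.01 | 1000 | 1.8 vs 1.4 | 6.6% | 4.9% |
| 0.01 | 1000 | 2.0 vs 1.3 | 14.6% | 5.1% |
| 0.01 | 3000 | equal | 5.0% | 5.2% |
| 0.01 | 3000 | 1.8 vs 1.4 | 11.9% | 4.6% |
| 0.01 | 3000 | 2.0 vs 1.3 | 35.6% | 4.8% |
| 0.03 | 1000 | equal | 4.9% | 4.9% |
| 0.03 | 1000 | 1.8 vs 1.4 | 12.2% | 4.9% |
| 0.03 | 1000 | 2.0 vs 1.3 | 33.8% | 4.4% |
| 0.03 | 3000 | equal | 4.5% | 4.4% |
| 0.03 | 3000 | 1.8 vs 1.4 | 27.8% | 4.6% |
| 0.03 | 3000 | 2.0 vs 1.3 | 77.6% | 5.1% |

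All hazards are equal, so every rejection is false. Wide variation in follow-up does no harm by itself. The damage comes from its association with group, and it grows with sample size and event rate.

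**The case against.** The strongest reply is that the article never assigns these events to chi-squared tests. Data analysis does not name them, Major secondary outcomes names no test, and emergency visits and admissions are naturally counts. This is correct. A reader might infer a deliberate assignment, but the events fall under the test only through the general rule, and only the yes/no events fall under it clearly.

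Secondly, a reader might infer that unequal follow-up must appear as risk. It need not: the equal-follow-up rows stay near 5%. A reader might also suppose that enrolment timing follows recruitment channel or site. The article lists channels and mentions satellite sites, but does not say when each recruits.

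Thirdly, larger effects can be produced. With h = 0.02, 1000 per group and 2.25 versus 0.75 years, the risks are 4.4% and 1.5% and the test rejects 97% of the time. That requires the exposure to coincide with early versus late enrolment, which is close to a worst case.

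Fourthly, events also come from medical records, so skipping a continuing series need not shorten event follow-up. This weakens the route through voluntary continuation. It does not remove differences in entry date if records are read up to a common closing date.

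Fifthly, an article condenses, and an analysis plan may specify event models. Their absence alone would be no fault. What remains is a rule that is stated, is unqualified and is unsuited to these events; a plan using event models would have to depart from it.

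Finally, a reader might infer that undiagnosed cases will be counted as new onset. The article gives no case definition, so that cannot be said. It also collects the date of diagnosis. Only the ambiguity stands.

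**Conclusion.** The point holds in conditional form. The only committed rule for categorical outcomes ignores time at risk, follow-up varies by design, and applying the rule to cardiovascular events or new-onset diabetes can produce false associations where follow-up is associated with the exposure. Under the assumptions above, false rejection is 7% to 28% at a mean follow-up of about 1.8 versus 1.4 years and 15% to 78% at about 2.0 versus 1.3, against about 5% for a person-time test.

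These figures rest on assumed hazards, group sizes and follow-up splits. They treat people as independent, so they say nothing about clustering within families. The primary outcome, establishing the cohort, is not affected. The new-onset diabetes definition is a secondary point.

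**What to change.** Amend the Data analysis text before any event comparison is made:

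- Limit chi-squared tests to baseline categorical variables, or to variables assessed at a fixed time for everyone.
- Analyse cardiovascular events and new-onset diabetes as time to first event (Cox).
- Analyse emergency visits and admissions as rates, by Poisson or negative binomial regression with a log person-time offset.
- Count time from enrolment to the last record extract or contact, and cluster standard errors on family.
- For new-onset diabetes, separate adults whose first study HbA1c or glucose is already in the diabetic range from incident cases. For children, whose laboratory tests are optional in Table 1, do this only where a baseline test exists and report the others separately.

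The cost is wording and slightly more analysis work. Event dates must be recorded, which the article does not state is done. Fewer cases will count as new onset, and children without a baseline test will form a separate group.

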### Aims

*The primary objective of this study is to determine the influence of the 5 major determinants of human health (genetics, biology, behavior, psychology, society/environment) on the real-world burden of T2D for Latino families.* To achieve this objective, beginning February 2019, Mil Familias (www.milfamilias.sansum.org/) began the establishment of an observational cohort of 1000 Latino families with at least one family member currently living with T2D, among whom we are studying the impact over time of the 5 main determinants of human health. We work with specially trained, bilingual Latino/a community health workers (known as Especialistas) who recruit participant families, conduct research activities including data collection, and, when necessary, refer families to appropriate community resources. Facilitated by these Especialistas, each individual family member contributes data annually on over 100 different variables relating to their genetics, biology, psychology, behavior, and society/environment, creating a Latino-focused biobank (“Living Information Bank”). Once the cohort is established, data analyses will inform the development of evidence-based, collaborative, and culturally-relevant prevention and treatment strategies.

An operational pilot involving over 100 adult Latino individuals with T2D, completed in 2018, established the feasibility of methods and created the infrastructure to scale to the 1000-family cohort (Mil Familias-Santa Barbara’s Operational Pilot to Understand Diabetes in the Latino Community NCT03736486).

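### The plan commits only to unadjusted tests and leaves covariate adjustment optional, although its objective calls for adjusted estimates

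*Protocol article*

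**What the plan says.** The Aims section of the protocol article states: "The primary objective of this study is to determine the influence of the 5 major determinants of human health", with T2D burden in Latino families as the target. The Discussion of the abstract and the Limitations section add a further question: whether cardio-metabolic risk extends past the usual biological and genetic factors.

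The Data analysis section sets the threshold: "All statistics will be considered significant with *p* values < 0.05". It then makes three firm commitments. The first reads: "Chi squared tests will be conducted to detect differences in categorical outcomes". The other two are for continuous outcomes: t-tests if any subgroup has fewer than 50 people, and Z tests above that size unless normality is in doubt.

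The next paragraph accepts that the independent variables may confound each other. What follows is worded as possibility. On confounding the commitment is that "consideration will be given to explore likely confounders". Propensity matching is mentioned as one example of an available method. The sentence on modelling is no firmer: "Regression analysis for a particular outcome can also be performed on various individual characteristics". No confounder is named, and no adjusted analysis is committed to.

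**The concern.** The analysis that the objective needs is the one left optional. Whether a social, psychological or behavioral variable matters in addition to biology and genetics is a conditional question. A test of one variable against one outcome does not answer it at any sample size.

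If the firm commitments alone are carried out, part of the effect of age, gender or time since diagnosis can be credited to a determinant that merely varies with them. A larger cohort does not help: the bias stays the same while the standard error shrinks, so a spurious association becomes more certain to be declared. The section's closing paragraph looks forward to significant results for most individual variables, so these are the results likely to be reported.

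**Working it through.** **Plan's own figure.** There is none on this point. The documents give no correlation between any determinant and a confounder, or between a confounder and an outcome. The pilot p-values in the Data analysis section concern something else.

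**Inputs from the protocol article**
- Threshold 0.05 (Data analysis). Sidedness is not stated; two-sided is assumed here.
- n=1000, the size used in the section's own power statement, and n=280, the larger of its two projected sizes.
- n=3000 = 1000 families × 3 people, the low end of the 3 to 5 per family in Setting and participants. This treats relatives as independent, so it is an upper indication.
- Age and gender are collected (Table 2), as is date of diabetes diagnosis (Table 1). Duration follows from the last, for participants with diabetes only.

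**Assumption.** One confounder correlates r with the determinant and r with the outcome, and the determinant has no effect of its own. r is varied from 0.1 to 0.3.

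**Formulas**
- Induced correlation: ρ = r² for a continuous determinant; ρ = r² × √(2/π) = 0.798 r² if the determinant is split 50/50 (r then refers to the variable before the split).
- Shift of the test statistic: δ = atanh(ρ) × √(n−3).
- Rejection rate: Φ(δ−1.96) + Φ(−δ−1.96).

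**At n=1000** (√997 = 31.58)

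| r | ρ, continuous | δ | Rejects | ρ, binary | δ | Rejects |
|---|---|---|---|---|---|---|
| 0.1 | 0.0100 | 0.32 | 6.1% | 0.0080 | 0.25 | 5.7% |
| 0.2 | 0.0400 | 1.26 | 24.4% | 0.0319 | 1.01 | 17.2% |
| 0.3 | 0.0900 | 2.85 | 81.3% | 0.0718 | 2.27 | 62.2% |

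**Other sizes** (binary to continuous)

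| r | n=280 | n=3000 |
|---|---|---|
| 0.1 | 5.2–5.3% | 7.2–8.5% |
| 0.2 | 8.3–10.2% | 41.6–59.1% |
| 0.3 | 22.4–32.4% | 97.6–99.9% |

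**Several confounders.** With three independent confounders of equal strength, ρ = 3r². At n=1000 the rate is 5.4–5.6% for r=0.05, 11.8–15.7% for r=0.1 and 85.8–96.8% for r=0.2.

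**Check by simulation** (1500 data sets per setting, binary determinant, one confounder)

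| n | r | Unadjusted | Adjusted regression |
|---|---|---|---|
| 280 | 0.1 | 6.0% | 5.3% |
| 280 | 0.2 | 8.0% | 4.9% |
| 280 | 0.3 | 21.3% | 5.4% |
| 1000 | 0.1 | 6.2% | 5.8% |
| 1000 | 0.2 | 18.1% | 5.7% |
| 1000 | 0.3 | 61.4% | 5.1% |

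The simulation error at a true rate of 5% is √(0.05 × 0.95 / 1500) = 0.6 percentage points. The adjusted rates are therefore compatible with 5%, and the unadjusted rates agree with the formula.

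**The case against.** The strongest reply is that the plan does not overlook confounding: it names the problem and mentions both regression and propensity matching. This is a condensed article, and a list of covariates per model belongs in a statistical analysis plan that is not shown. The stated primary outcome is the creation of the cohort, not a test of any determinant.

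Much of this is fair. A reader might infer that the plan ignores confounding, or that no adjusted analysis will be done; the text supports neither. The absence of a covariate list is not the point. What remains is the order of commitment: the article gives the firm promise to the unadjusted tests and the optional wording to the adjusted ones. That is a stated choice of inferential method, and it does not fit the stated objective. The primary outcome limits how serious this is but leaves the objective in place.

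Other tempting readings also go too far:
- That null determinants will often come out significant. With one weak confounder (r=0.1) the rate at n=1000 is close to nominal.
- That 81% is the expected rate. It needs r=0.3 on both sides and a continuous determinant; a binary one gives 62%.
- That the committed tests all compare two groups. Chi-squared tests are not so limited; unadjusted is the accurate description.
- That propensity matching is the chosen method. It appears only as an example. It fits binary exposures better than graded scales, but nothing in the text makes it the default.
- That one joint model of all five domains would settle the matter. Biological or behavioral variables may lie on the path from social or genetic factors to HbA1c, and adjusting for them could remove part of the influence being sought.

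**Conclusion.** The point holds as a mismatch between objective and committed analysis. Unadjusted tests can declare null determinants significant, to an extent that the documents do not allow one to fix. At n=1000 and a nominal 5%, one confounder raises the rate to about 6% (r=0.1), 17–24% (r=0.2) or 62–81% (r=0.3), and the rate grows with n. These figures rest on assumed correlations, a two-sided test, independent participants and a determinant with no true effect. Adjustment restores about 5% only for a confounder that is measured and in the model; confounding from other sources would remain. The sponsor should make the change: it affects the main inferential aim and costs little. It is not more serious than that, because adjustment is contemplated and the primary outcome is establishing the cohort.

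**What to change.** Reword the Data analysis section as follows:

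1. The main analysis of each determinant–outcome association is a regression adjusted for at least age and gender, plus diabetes duration among members with T2D.
2. The model has a family random effect, because co-resident relatives are enrolled together. This deals with clustering, not confounding, but belongs in the same model statement.
3. Chi-squared, t and Z tests are kept as descriptive.
4. Propensity matching remains an option for binary exposures.
5. Any joint five-domain model is secondary, with a note that it may adjust for mediators.

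The cost is a rewritten section and slightly more analysis work. The covariates are already listed in Tables 1 and 2 and family membership is already recorded, so no new data collection is needed.
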